### Strategies to improve adherence to interventions {11c}

Adherence during the treatment phase will be monitored as follows: (a) Participants will receive a phone call from a team member providing all the important information (e.g. sessions schedule and calendar, local/link where the intervention takes place, facilitators’ names and contacts), followed by an email with the same details. (b) They will also receive a reminder of the upcoming session by email a few hours before the meeting and by phone call/text message just before the session. (c) Materials for between-session assignments (homework) will be sent by email immediately after each Mind programme session and a reminder reinforcing at-home practice will follow through the same channel 2–3 days after.

### Relevant concomitant care permitted or prohibited during the trial {11d}

Women receiving any form of psychotherapy at screening are not eligible. However, participants are not prohibited from seeking other interventions or treatment during their participation in the trials. Engagement in any other intervention or treatment must be reported to the research team during their participation.

### Provisions for post-trial care {30}

Adverse events are not expected (see Sect. 22). Therefore, there are no provisions for any additional post-trial care or to provide compensation to those who suffer harm from trial participation.

**Table 3 Tab3:**
[figure not shown]
Schedule of enrolment, intervention and assessments for study 1 and study 2

Note. EORTC QLQ-C30, QLQ-BR23, The European Organization for Research and Treatment of Cancer Quality of Life Questionnaire and its Supplementary Questionnaire Breast Cancer Module, HADS, The Hospital Anxiety and Depression Scale, CompACT, Comprehensive Assessment of Acceptance and Commitment Therapy processes, SCS, Self-Compassion Scale, EQ-5D-5L, health-related quality of life

**only for study 2 participants

*only for study 1 participants

only for a subsample of study 1 participants

†only for intervention groups

only for Mind participants

### Participant timeline {13}

See Table 3.

### Sample size {14}

Regarding study 1, power was considered according to a sensitivity analysis of the likely attainable sample size and compare with the effect sizes estimated by previous meta-analyses and studies suggesting improvements in mood and QoL between SMD = 0.2 to 0.6, favouring psychotherapies over controls [15, 16]. It is anticipated that up to *N* = 150 (*n* = 75 per group) participants will be recruited, and attrition rates of between 10 and 30% can be expected. The planned analysis specifies a repeated-measures linear mixed models analysis, a group allocation of 1:1, alpha of 0.05, a minimum of 80% power, three assessment points and a compound symmetry correlation matrix (rho = 0.5; Lu et al., 2008). Under these parameters, the study is powered to reliably detect a between-group difference on cancer-specific QoL at follow-up of SMD = 0.51 (WebPower; [37]).

For study 2, the GLIMMPSE software was used to calculate the minimum sample size required for a three-armed linear mixed model with three measurements. Assuming a comparable effect size to that estimated in study 1 (SMD = 0.5) favouring the Mind intervention group over waiting list at 6 months for QoL, an unstructured correlation matrix, a group allocation of 2:2:1, alpha of 0.05 and a minimum of 80% power, the minimum sample size required is *N* = 117. To account for up to 30% attrition, this sets the minimum total sample size at *N* = 153 [38].

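### Study 2's N = 117 cannot be reproduced as 80% power for Mind v waiting list at 6 months; at a correlation of 0.5 that contrast has about 50% to 62% power

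*Protocol article*

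**What the plan says.** All the figures are in the protocol article, Sample size {14}.

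- **Study 1.** Up to 150 women at 1:1, attrition of 10% to 30%, alpha 0.05, 80% power, and "three assessment points and a compound symmetry correlation matrix (rho = 0.5; Lu et al., 2008"). The stated result is a detectable between-group SMD of 0.51 at follow-up. Study 1's only comparator is the support group.
- **Study 2.** A separate GLIMMPSE calculation for a three-arm mixed model with three measurements. The effect is introduced as "Assuming a comparable effect size to that estimated in study 1 (SMD = 0.5"). The contrast, correlation structure and allocation are then given as "favouring the Mind intervention group over waiting list at 6 months for QoL, an unstructured correlation matrix, a group allocation of 2:2:1". Alpha is set at 0.05 and power at no less than 80%. The conclusion is that "the minimum sample size required is *N* = 117", raised to 153 for attrition.

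For Study 2 the article prints no correlation values, no sidedness, no assumed means for the support arm and no tested hypothesis beyond the named contrast. Statistical methods {20a} says Mind will be compared with both the support and waiting-list groups in Study 2. It calls the analytical approaches of the two studies otherwise comparable.

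**The concern.** At 2:2:1 only three fifths of the sample enters the Mind v waiting-list contrast, and the smaller arm holds one fifth. About 70 women split 2:1 are therefore said to detect 0.5, while in the same section 150 women less attrition, split equally, are said to detect 0.51. Both statements can hold only if Study 2 used much more favourable correlations or tested something else, and the text says neither.

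The waiting-list arm is what distinguishes Study 2's design, and superiority over it is one of the planned comparisons. If power for that contrast is nearer one half than 80%, a non-significant result says little about the programme, and readers relying on the stated power could take it to say more.

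The source of the 0.5 is also misdescribed. A minimum detectable difference is a property of a sample size, not evidence about an effect, and Study 1's value concerns a different comparator.

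**Working it through.** **Inputs.** From Sample size {14}: N = 117, 2:2:1, SMD 0.5 (SD = 1), alpha 0.05, 80% power, Mind v waiting list at 6 months. Assumed here: a two-sided test, and a baseline-to-6-month correlation ρ, which Study 2 does not print.

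**Arms.** 0.4 × 117 = 46.8 and 0.2 × 117 = 23.4, so 1/46.8 + 1/23.4 = 0.0641.

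**Formula.** SE = √(v × 0.0641), with power from the noncentral t at 0.5/SE. The variance factor v is 1 for the raw 6-month comparison, 2(1 − ρ) for change from baseline and 1 − ρ² for baseline-adjusted.

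**Named contrast at ρ = 0.5**
- Raw or change score (v = 1): SE = 0.253, 0.5/0.253 = 1.97, power about 50%.
- Baseline-adjusted (v = 0.75): SE = 0.219, 0.5/0.219 = 2.28, power 61% to 62%.
- Detectable SMD with 80% power: about 0.72 and 0.62 respectively.
- One-sided testing, which the article does not state, gives about 62% and 73%.

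**Total N for 80% at ρ = 0.5.** Since 1/(0.4N) + 1/(0.2N) = 7.5/N, N ≈ 7.849 × v × 7.5/0.25. That is 235 for v = 1 and 177 for v = 0.75, or about 240 and 180 after the t correction and rounding. The stated 117 is not reproduced.

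**Dependence on ρ at N = 117**

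| ρ | Change score | Baseline-adjusted |
|---|---|---|
| 0.3 | 38% | 54% |
| 0.5 | 50% | 62% |
| 0.6 | 59% | 69% |
| 0.7 | 72% | 78% |
| 0.75 | 79% | 84% |
| 0.8 | 87% | 90% |

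Power reaches 80% at ρ of about 0.76 (change score) or 0.72 (baseline-adjusted).

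**Hypotheses that come close to 117 at ρ = 0.5**
- Mind v support (46.8 v 46.8), baseline-adjusted: N = 7.849 × 0.75 × 5/0.25 = 117.7; power at 117 about 79%.
- Mind v waiting list averaged over post-treatment and 6 months, baseline-adjusted, SMD 0.5 at both times: v = (1 + ρ)/2 − ρ² = 0.5; N = 7.849 × 0.5 × 7.5/0.25 = 117.7; power at 117 about 79%.
- Omnibus three-arm test at 6 months, baseline-adjusted, support set equal to waiting list: noncentrality 7.02/0.75 = 9.36 on F(2,114); power 78%. With support halfway between the other arms it is 53%.

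None of these is the named 6-month contrast.

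**Check against Study 1, without choosing ρ.** Its 0.51 is matched at 80% by 60 per arm (150 less 20%) with v = 1. Scaling by the standard errors, the same basis gives Study 2 a detectable SMD of 0.51 × √(0.0641/0.0333) = 0.71. If the 0.51 refers instead to 52.5 or 75 per arm, the result is 0.66 or 0.79.

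**After attrition.** 153 less 30% is about 107. Power for the named contrast at ρ = 0.5 is then about 46% (raw or change score) or 57% (baseline-adjusted). With all 153 analysed it is 61% or 73%.

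**The case against.** The strongest reply is that 0.5 is Study 1's correlation. Study 2 was calculated in different software with an unstructured matrix, and nothing in the text carries 0.5 across. A reader might infer from the low figures that 117 simply fails to give 80% power. The documents do not support that: correlations of about 0.72 to 0.76 or more would give it, and the article neither states nor excludes them. This stands, so the power figures here are conditional on ρ.

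A reader might also infer that 117 came from an omnibus test. That is not established. Mind v support, and Mind v waiting list averaged over the two post-baseline times, come at least as close. The averaged contrast uses the named pair of arms within a repeated-measures model, which is the kind of model said to have been powered.

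A third point is that an article condenses its protocol, so the GLIMMPSE inputs may be recorded elsewhere. Their absence is therefore not the finding. What remains is that a contrast, an N and a power are printed together and do not agree unless the correlation is well above the only one printed.

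Finally, 0.5 lies within the 0.2 to 0.6 range that the section cites from earlier work. It is admissible as an assumption; only its description as a Study 1 estimate is wrong.

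**Conclusion.** The point holds in conditional form. N = 117 at 2:2:1 is not reproducible as 80% power for Mind v waiting list at 6 months with SMD 0.5, two-sided. It requires a baseline-to-6-month correlation of about 0.72 (baseline-adjusted) or 0.76 (change score). At 0.5, power is about 50% to 62%, and an 80% claim would need a total of about 240 or 180 analysed women. The Study 1 comparison points the same way without a choice of correlation, provided the two trials share the same variance basis. Which hypothesis produced 117 cannot be settled from the article.

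The description of 0.5 as estimated in Study 1 is wrong as written, whatever the correlation.

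**What to change.** In Sample size {14}, for Study 2:

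1. Give the power, or the SMD detectable with 80% power, separately for Mind v waiting list at 6 months and for Mind v support, at the expected analysable N.
2. State the correlations, the assumed support-arm means, the sidedness and the hypothesis tested in GLIMMPSE.
3. If 117 came from another hypothesis, or from correlations that cannot be justified, say so and drop the 80% claim for Mind v waiting list.
4. Describe 0.5 as an assumed effect, and describe Study 1's 0.51 as a minimum detectable difference against the support group.

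The cost is a revised paragraph and probably a less favourable stated power. No extra patients and no change of design are requested.

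### Study 2's minimum of 153 does not absorb the stated 30% attrition on a required 117; it covers about 23.5%, and 30% would need 168

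*Protocol article*

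**What the plan says.** The second paragraph of Sample size {14} in the protocol article sizes study 2 with GLIMMPSE for a three-arm linear mixed model with three measurements. The target is a standardised mean difference of 0.5 for Mind over waiting list in quality of life at 6 months. The other settings are "an unstructured correlation matrix", whose values are not given, and "a group allocation of 2:2:1, alpha of 0.05 and a minimum of 80% power". From these, "the minimum sample size required is *N* = 117".

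The next sentence makes the allowance for dropout: "To account for up to 30% attrition, this sets the minimum total sample size at" 153. The formula for this step is not written out.

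**The concern.** Attrition is a loss from the women enrolled. A total that allows for 30% attrition must therefore still leave the required number after 30% of that total has gone. The stated 153 looks as if 30% of the required number was added on top, which is a smaller allowance. If so, the minimum total and the attrition it is said to cover cannot both hold.

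The figure is in use. The article's Trials status {3} section puts the end of study 2 recruitment at an estimated March 2025, and Limitations lists the risk of dropout first. A team that stops at 153 would believe it has a 30% margin when it has less, and at the upper end of the stated attrition the trial would fall below its own requirement.

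**Working it through.** **Inputs, all from Sample size {14}, study 2:** required number 117; maximum attrition 30%; stated total 153; allocation 2:2:1; alpha 0.05; power at least 80%. The section does not say whether alpha is one- or two-sided; two-sided is assumed in step 5.

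**1. Reproduce the stated total.**
- Adding 30% to the requirement: 117 x (1 + 0.30) = 152.1, rounded up to **153**. This matches.
- Dividing by the proportion retained: 117/(1 - 0.30) = 167.14, rounded up to 168. This does not match.
- Rounding does not explain the gap. Starting from 115 or 120, division by 0.7 gives 164.3 or 171.4. Rounding each arm up first (47/47/24) and dividing by 0.7 gives 68 + 68 + 35 = 171.

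None of the division variants tried at 30% gives 153. That 117 was multiplied by 1.3 is an inference, since the formula is not printed. Steps 2 to 4 hold however 153 was reached.

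**2. What 153 leaves at 30% attrition.** 153 x 0.7 = 107.1, so about 107 completers. The shortfall is 117 - 107 = 10, or 10/117 = 8.5%. One fifth of the total is the waiting-list arm, which falls from 117/5 = 23.4 to 107/5 = 21.4.

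**3. What attrition 153 does cover.** 1 - 117/153 = 0.235. For example, 20% attrition leaves 153 x 0.8 = 122.4, which is enough; 25% leaves 153 x 0.75 = 114.75, which is not.

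**4. What 30% attrition requires.** 117/0.7 = 167.14, so 168 women, or 170 for whole 2:2:1 blocks (68/68/34). Check: 168 x 0.7 = 117.6 and 170 x 0.7 = 119. These totals are 15 and 17 above 153.

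**5. Effect on power.** Assume that 117 gives exactly 80% power, two-sided alpha of 0.05, a normal approximation, and power that depends only on the number of completers. The noncentrality at 117 is 1.960 + 0.842 = 2.802. It scales with the square root of the number:

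power at 107 = Φ(2.802 x √(107/117) - 1.960) = Φ(2.679 - 1.960) = Φ(0.719) ≈ 0.76.

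On these assumptions the loss is about 4 percentage points.

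**The case against.** **Partial data are used.** The article plans a repeated-measures linear mixed model (Aim 1 in section {20a}), intention-to-treat analysis with multiple imputation or full information maximum likelihood (section {20c}), and continued data collection after a woman stops the intervention (section {18b}). A woman who misses the 6-month assessment can still contribute earlier data. This stands: 107 counts completers, not everyone in the analysis, and 76% is probably pessimistic. It does not rescue the sentence, because the inflation was made to preserve 117 and does not do so at the attrition named. The contrast used for sizing is also at the last visit.

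**30% is a ceiling, not a forecast.** For study 2 the section gives only an upper limit; the expected range of 10 to 30% is stated for study 1. This also stands. The shortfall arises only between 23.5% and 30%, so a reader should not infer that study 2 will miss its requirement at the attrition the protocol expects. The ceiling is nevertheless what the total is said to cover.

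**153 is a minimum, so recruiting more is possible.** True, but the stated minimum is still wrong for its stated purpose. The source cited beside the figure is not available here, but it could not change the arithmetic.

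**A stronger reading about power.** A reader might apply a within-person correlation of 0.5 to Mind against waiting list with 107 completers, obtain about 46% power unadjusted or 57% baseline-adjusted, and blame the inflation step. The documents do not support that. The correlation of 0.5 is stated for study 1, while study 2 has an unstructured matrix with no values. The same calculation at the full 117 gives 49% and 61%, so only about 3 to 4 points come from the inflation. The rest concerns whether 117 is a sound base. That is a separate question, and it cannot be checked without the correlations and the exact hypothesis entered in the software.

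**The small waiting-list arm.** Its size mainly reflects the 2:2:1 ratio, chosen deliberately in Trial design {8}. The inflation step costs that arm about two women.

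**Conclusion.** The sentence is wrong as written. On the protocol's own figures, 153 absorbs up to about 23.5% attrition, not 30%, and covering 30% takes 168 women (170 for whole 2:2:1 blocks). This conclusion takes 117 as given and needs no other assumption.

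The practical effect is small. At the maximum attrition named there would be about 107 completers against 117. Power would fall from 80% to about 76% if 117 is valid and only completers count, and probably by less under the planned analysis. The error leaves the outcome, the comparisons and the method of analysis unchanged. It should be fixed, and nothing here justifies calling study 2 badly underpowered.

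**What to change.** Restate the attrition sentence in Sample size {14} in one of two ways:

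- **Keep 153** and say that it retains 117 up to about 23.5% attrition. Add that at 30% about 107 completers would remain, with about 76% power if 117 gives 80% and only completers count.
- **Keep the 30% allowance** and give 168, or 170 for whole 2:2:1 blocks, as the minimum total.

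In either case, show the formula: required number divided by one minus the attrition proportion.

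The first option costs a sentence and a less favourable stated margin. The second means recruiting 15 to 17 more women than 153. Neither requires a change to the analysis.

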### Recruitment {15}

In study 1, women being treated for BC in the Radiotherapy Service of CHUC will be invited to participate. The point of recruitment will be at the beginning of radiotherapy treatment. The trial will be introduced to potential participants by their radiotherapy physician. A screening interview will be conducted with interested patients to assess eligibility and obtain written informed consent.

In study 2, the trial will be disseminated among the Portuguese population via press releases, social media platforms (e.g. postings with relevant groups and communities via Facebook and Instagram) and BC patients’ associations electronic distribution lists. Women with BC will register their interest by completing a form hosted on a secure online platform, which can be easily found in the project’s website. Alternatively, interested persons can contact research staff via email provided in the study advertisements. A screening interview, conducted by phone call, is later conducted to assess eligibility and obtain electronic informed consent.

## Assignment of interventions: allocation

### Sequence generation {16a}

Computer-based randomisation will be used (www.random.org/lists/), via a numbered sequence, in both studies, by blinded researchers. Allocation of women who underwent chemotherapy and those who did not will be proportionate among the groups (stratified randomisation).

### Implementation {16c} and concealment mechanism {16b}

After sample selection and filling of the baseline measures, participants will be randomly allocated to one of two (study 1) or three (study 2) conditions: (a) experimental group (Mind programme), (b) active control group (support group) and (c) inactive control group (treatment as usual; study 2 only). Allocation and assignment of participants will be conducted by members of the research team who do not have access to participants’ information other than study identification code and chemotherapy status.

### Procedure for unblinding if needed {17b}

Staff members whose role is to contact participants before and throughout the intervention phase will not be blinded to the treatment assignment. In the unlikely event that an adverse event should occur, unblinding of other members and of participants can take place.

## Data collection and management

### Plans for assessment and collection of outcomes {18a}

Outcome self-report measures will be completed independently by participants, reducing risk of bias. These measures will be hosted on LimeSurvey, a secure web-based data collection platform. A description of all research measures follows (see Table 3 for assessment timing).

### Primary outcome

#### Cancer-specific QoL

The European Organization for Research and Treatment of Cancer Quality of Life Questionnaire (EORTC QLQ-C30; [39]; Portuguese version: [40]) is a 30-item questionnaire that reflects the multidimensionality of the QoL construct, comprising five functional subscales (physical, role, cognitive, emotional and social); a global health/QoL subscale; three symptom subscales (fatigue, pain and nausea/vomiting); single items for the assessment of additional symptoms commonly reported by cancer patients (dyspnoea, appetite loss, sleep disturbance, constipation and diarrhoea); and one more item related to the perceived financial impact of cancer and cancer treatment. All the items are scored on a 4-point Likert type scales ranging from 1 (not at all) to 4 (very much), except the two items of the global health/QoL subscale, which use a modified 7-point linear analogue scale. The 23-item Supplementary Questionnaire Breast Cancer Module (QLQ-BR23) additionally assesses body image, sexual function, sexual enjoyment and future perspective. In the Portuguese validation study, global QoL presented a Cronbach’s alpha of 0.88 and the different subscales presented Cronbach’s alpha ranging between 0.57 and 0.88 [41].

### Secondary outcomes

#### Anxiety and depressive symptoms

The Hospital Anxiety and Depression Scale (HADS; [42]; Portuguese version: [43]) is a 14-item self-report questionnaire that includes two subscales, one measuring anxiety and one measuring depressive symptoms, which are scored separately. Each item is rated on a 4-point scale from 0 (no impairment) to 3 (severe impairment). In the Portuguese validation study, the anxiety and depression subscales had Cronbach’s alpha values of 0.76 and 0.81, respectively.

#### Psychological flexibility

The Portuguese Comprehensive Assessment of Acceptance and Commitment Therapy processes (CompACT; [44]; Portuguese version: [45, 46]) is a measure of psychological flexibility, as conceptualised by ACT. Items are rated on a 7-point Likert scale from 0 (never true) to 6 (always true). The Portuguese validation of the CompACT in illness resulted in an 8-item version.

#### Self-compassion

The Self-Compassion Scale (SCS; [47]; Portuguese version: [48]) is a 26-item instrument with six subscales to assess self-compassion: self-judgement, self-kindness, overidentification, mindfulness, isolation and common humanity. Items are rated on a 5-point Likert scale from 1 (almost never) to 5 (almost always). The Portuguese study of the SCS presented a Cronbach’s alpha of 0.94 for the total scale, and alphas between 0.70 and 0.88 for the subscales.

#### Health-related QoL

The EQ-5D-5L ([49]; Portuguese version: [50]) is a generic instrument for assessing health-related QoL in economic evaluation. It is a self-report questionnaire with five items/dimensions (mobility, self-care, usual activities, pain/discomfort and anxiety/depression) and one visual analogue scale to assess self-rated health status. For each dimension, participants select one of five levels: 1 (no problems), 2 (slight problems), 3 (moderate problems), 4 (severe problems) and 5 (extreme problems). Scores will be converted into utility weights using the value set estimated for Portugal to obtain a single summary index ranging from 0 (death) to 1 (perfect health). In addition, the visual analogue scale records the patient’s self-rated health state, between 0 (the worst health you can imagine) and 100 (the best health you can imagine). In the Portuguese validation study, the EQ-5D showed a Cronbach’s alpha of 0.72.

